**Figure 1 figure1:**
[figure not shown]
SPIRIT (Standard Protocol Items: Recommendations for Interventional Trials) schedule of enrollment, interventions, and assessments. SM: self-management; PA: physical activity.

### Randomization

The unit of randomization will be the participant, and the randomization process will use computer generation of group assignment using the REDCap (Research Electronic Data Capture; Vanderbilt University) randomization module. REDCap is a secure web application designed to support data capture for research studies [91]. Participants will be stratified by age (55-64 years or 65-75 years). An allocation table will be created and uploaded to the REDCap randomization module by a statistician not involved in the RCT. Using a 1:1:1 allocation ratio, we will block the randomization with variable block sizes of 3, 6, and 9. The RC will not have access to the allocation table. Once participant consent is obtained and the baseline assessment is complete, the RC will access the randomization module in REDCap to enter the participant strata value (age category) and receive the group allocation.

### Data Collection and Management

During an introductory Zoom session with each participant, the RC will discuss space requirements and setup for the assessments and review emergency procedures should an adverse event occur. Written instructions will be sent by email before each assessment. The instructions will describe the setup required for the assessment and a list of equipment needed (measuring tape, chair, and masking tape to mark distances). If the participant is unable to secure these items independently, they will be mailed to them before their baseline assessment.

The same physiotherapist blinded to group assignment will perform baseline and follow-up assessments for a given participant. All trial assessments will be conducted virtually using the Zoom platform. During the assessments, assessors will use screen-sharing to administer patient-reported questionnaires and enter participant responses directly into REDCap. For the performance measures, assessors will use screen-sharing to play a video clip to demonstrate how the participant is expected to complete each of the physical tests that will be administered. Participants will then complete each test with the assessor observing by video, and scores will be entered into REDCap.

We have estimated the rate of loss to follow-up in our sample size calculation as 20%. We will attempt to minimize loss to follow-up in the trial by using a 2-stage screening process and by having the RC follow-up with participants after 2 consecutive unreported absences. Participants who drop out of their intervention will be given the opportunity to complete follow-up assessments. Those participants who complete follow-up will also be offered a personalized report that provides them with a summary of their results.

Intervention-specific data will be entered into REDCap by trained study staff or by survey. The physiotherapist delivering the telephone-based coaching walking intervention will enter data pertaining to the participant’s goals and action plans during the weekly telephone sessions. Participants in the Stepping Up intervention will receive weekly REDCap surveys and will record their goals, action plans, and practice minutes. The RC will perform regular checks to ensure completeness and will follow-up on any missing data.

Personal information will be collected directly from each participant by the RC during the introductory Zoom session. Personal information (name, address, phone number, and phone number of an emergency contact) will be shared with the assessors using a private Google Calendar and with the study staff delivering the interventions using encrypted email. Participant data will be deidentified using a study ID number. A password protected electronic file linking participant identifiers to their study ID number will be stored on a secure server. Only the Primary Investigators and the RC will have access to this file. Additionally, only the primary investigators and authorized users will have access to the project in REDCap. User rights will be configured to ensure that users only have access to the data essential to their role.

### Analysis

Baseline characteristics will be analyzed using descriptive statistics reported as mean (SD) or median (first quartile {Q1}, third quartile {Q3}) for continuous variables, depending on the distribution and count (%) for categorical variables. All analyses of primary and secondary outcomes will follow the intention-to-treat principle. The results will be reported as relative risk or odds ratio for binary outcomes or mean difference for continuous outcomes, with corresponding 95% CI and associated *P* values. All *P* values will be reported to 3 decimal places with those less than .001 reported as *P*<.001. All analyses will be performed using SAS 9.4. We will use multiple imputation to handle missing data [92].

To assess the effect of the intervention on the primary outcome (4MGS), we will conduct an analysis of covariance adjusting for age as a stratification variable and baseline value of 4MGS as a covariate. Secondary outcomes will also be analyzed using analysis of covariance, again using age as a stratification variable and baseline value for each outcome as a covariate. No interim analysis is planned.

We will conduct exploratory subgroup analysis for both the primary and secondary outcomes by including an interaction term between the subgroup variable (sex and age) and the treatment group variable. The multiple measures subgroup analyses will not be adjusted for multiple testing since they are exploratory.

Our hypothesis is that there will be reduced hospitalizations and physician visits for the intervention group compared with the control groups. Cost data is usually treated as nonparametric. Therefore, a Poisson or negative binomial distribution will be used to model the number of hospitalizations and physician visits by counts to determine the difference between the groups on relative intervention cost.

Analysis of the qualitative interview transcripts will follow an interpretive descriptive approach [90], an approach used in applied health disciplines to inform practice. A member of the research team will lead the analysis involving: (1) multiple line by line readings of the data to ensure a deep understanding of the data; (2) an inductive and deductive coding process based on the research questions and the emerging analysis; (3) the use of a data matrix to facilitate the manipulation of coded data and exploration of patterns, variations, and discrepancies, as well as comparisons within and among the participant groups in the data; and (4) finally, asking questions of the data to understand aspects of intervention and to answer the research questions. Rigor will be enhanced by the maintenance of a detailed record of all steps [93], inclusion of multiple perspectives in the analysis [94], guidance of a methodological framework [90], and use of the NVivo qualitative data analysis software (Lumivero) [95].

The cost-effectiveness analysis will compare the Stepping Up program with the telephone-based coaching walking program and the chair-based yoga program from the public health care payer’s perspective. The main effectiveness measure for the cost-effectiveness analysis will be the incremental cost per QALY gained over 36 weeks. We consider 36 weeks’ sufficient time to capture the potential cost-effectiveness of Stepping Up. As this cost-effectiveness analysis is conducted alongside the trial, nonparametric bootstrap will be used to calculate the 95% CI around the incremental cost per QALY ratio. The decision uncertainty will be presented using cost-effectiveness acceptability curves, which show the probability of the intervention being cost-effective compared with the telephone-based coaching walking group and the chair-based yoga group.

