PCML manifests early in the process of declining mobility and is not typically identified or acted upon by clinicians. The prevalence of PCML in community dwelling samples ranges 20%-40% [15] and 31%-55% in adults over 75 years [16]. These mobility limitations manifest as changes in how daily tasks such as walking are performed (slower speed and lower endurance). Persons with PCML are at increased risk for the onset of disability and chronic disease [17,18]. Persistent deterioration in mobility is a predictor of mortality and has been reported even in the absence of changes in activities of daily living over a two-year period [19]. Further, older persons with mobility limitations, including reduced gait speed, are at risk for falls [4,20]. Thus, PCML is a critical stage in the natural history of functional change with aging when there is the opportunity for primary prevention interventions [21,22].

Interventions to improve walking (gait) are usually impairment-focused, aimed to address issues such as strength, flexibility, and endurance [23]. However, recent evidence suggests that interventions aimed to optimize mobility in older adults must also address task-oriented motor sequence learning to improve walking skills [23]. Motor skill-based exercise needs to address several components to optimize benefits to walking ability that include (1) an identified movement goal, (2) movement that provides feedback about muscle ability, posture, and movement awareness, (3) repetition and practice to correct errors, and (4) altering the environment and practice conditions to select an optimal motor plan [23].

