### Objectives

Our primary objective is to determine if a 12-week mobility program called Stepping Up is more effective than a telephone-based coaching walking program or a chair-based yoga program at improving walking speed, assessed using the Four-Meter Gait Speed (4MGS) test. Secondary objectives are to compare the effectiveness of the Stepping Up program to the telephone-based coaching walking program and the chair-based yoga program for the following outcomes: (1) gait speed at 24 and 36 weeks and (2) aerobic exercise capacity, dual-task cost, physical functioning (balance and strength), balance confidence, extent of community mobility, SM of mobility, and quality of life at 12, 24, and 36 weeks.

We will compare the cost-effectiveness of the Stepping Up program to the telephone-based coaching walking program and the chair-based yoga program with respect to health care usage costs (including hospitalizations and physician visits) and program-related costs over 36 weeks.

Focus groups will be conducted to discover how participants in the Stepping Up program develop their mobility skills in comparison to those in the telephone-based coaching walking program and chair-based yoga program.

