### Interventions

The Stepping Up program is a 12-week, multicomponent intervention that includes tailored TOML exercise and a mobility SM program developed for the pilot study. Participants will attend two 1-hour synchronous online sessions (1-hour exercise and 1-hour SM) per week using Zoom. The exercise component includes a variety of stepping sequences that are intended to enhance timing and coordination and improve automatic control of walking. Timing and coordination problems impact walking efficiency and contribute to age-related decline in physical function for older adults. [24] The exercise program begins with simple stepping patterns and progresses over 12 weeks. Each participant has a card which indicates the tailoring to address individual difficulties and mastery of each stepping pattern, as well as the progression to increase the complexity. Progression involves introducing more complex stepping tasks (ie, diagonal patterns that require stepping across midline), as well as increasing speed and varying the base of support. Once a stepping pattern is mastered, a dual task is introduced (ie, carrying an object in one or both hands and performing a cognitive task). The online class will be led by a fitness instructor and monitored by a physiotherapist who will provide feedback and individually tailor the exercises for each participant. The mobility SM component, facilitated by a physiotherapist, will aim to enhance participants’ understanding of (1) changes in mobility with aging [17,34], (2) active SM of mobility including self-monitoring [27,28,34], (3) preclinical disability [17,18,35], (4) the importance of walking speed [2,23], (5) fall prevention [36], (6) exercise and TOML to improve mobility [25,37], (7) strategies to optimize sleep [38-40], (8) managing pain and physical discomfort [41,42], (9) conserving energy and minimizing fatigue [43], (10) better breathing [44], (11) posture to promote mobility [45,46], and (12) environmental barriers to walking and mobility [47,48]. The SM sessions were developed based on research evidence, discussion in an online forum with physiotherapists and researchers in mobility and aging, and in consultation with older adults. The SM component aims to increase self-efficacy through collaborative goal setting and action planning. A study website will allow participants to view short videos of the walking patterns being performed and review the SM sessions.

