We will incorporate two control groups to establish the true effect of the Stepping Up intervention. The telephone-based coaching walking program will act as a comparative effectiveness control group. A review of interventions to increase walking behavior found that telephone interventions as brief prompts appeared to be as effective as in-depth counseling supporting walking prescriptions of 5-7 days per week versus 3-5 days per week [49]. In these studies, telephone interventions were often added as an adjunct to the primary intervention and mobility was not always measured as an outcome. Telephone counseling, compared with no intervention, has been shown to increase physical activity in low-activity older persons recruited from primary care [50,51]. However, it is unclear whether telephone-delivered interventions are cost-effective compared with face-to-face interventions for improving walking in persons with PCML [52].

The telephone-based coaching walking program will be delivered by a physiotherapist. The frequency, duration, and intensity of walking will be determined based on the individual’s current level of physical activity and an end target level of physical activity (minimum of 150 minutes of moderate-intensity aerobic exercise per week) [53]. The physiotherapist will engage participants in goal setting and action planning, which will include discussion of coping, planning, identifying support systems, and evaluating self-efficacy. The initial telephone contact will last 20-30 minutes, and subsequent weekly calls will last approximately 10 minutes. Therapists will help participants evaluate their action plans, assist with problem-solving, discuss program progression, and help develop new action plans. This group will also receive written material about the benefits of walking and the importance of walking speed.

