The chair-based yoga program will act as an attention control group. Chair-based yoga programs are typically reserved for older adults who are unable to participate in regular exercise or standing yoga programs. An RCT evaluating an 8-week chair-yoga program for older adults with lower extremity osteoarthritis who could not participate in standing exercise found that participants experienced a reduction in pain and an increase in gait speed compared with those in a health education program [54]. These improvements were not sustained postintervention. Chair-based yoga has not been evaluated for effectiveness in improving mobility outcomes for higher-functioning older adults with PCML.

Participants in the chair-based yoga program will undertake chair-based yoga sessions that include breathing control, seated poses, standing poses, and relaxation exercises, led by a fitness instructor. Participants will join a synchronous online class for 1 hour, twice per week for 12 weeks.

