#### Sample Size

The sample size calculation is based on the primary outcome measure, the 4MGS test. Small clinically meaningful change is 0.05 m/second on the 4MGS test in older adults [2]. We expect to observe minimal to no change in the chair-based yoga group (0 m/s), small but meaningful change in the telephone-based coaching walking group (0.05 m/s), and a large change in the Stepping Up group (0.12 m/s) [61]. Assuming a correlation between baseline and 12-week scores of 0.5, a mean baseline gait speed of 1.14 m/second, and a common SD of 0.22, a sample size of 66 per group (N=198) will have 80% power at the 0.05 significance level. To account for dropouts (20%), the planned total sample size is 249 (or 83 per group). Sample size calculations were performed using SAS (version 9.4; SAS Institute).

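### The payer cost-effectiveness analysis uses the chair-yoga attention control as a comparator, apparently net of yoga's delivery cost; the three programmes should be analysed jointly

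*Protocol article*

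**What the plan says.** The Analysis section of the protocol article says: "The cost-effectiveness analysis will compare the Stepping Up program with the telephone-based coaching walking program and the chair-based yoga program". The perspective is that of the public health care payer, and the main measure is incremental cost per QALY over 36 weeks. Acceptability curves are to give the probability that the intervention is cost-effective compared with the two control groups. The Objectives section defines the costs as "health care usage costs (including hospitalizations and physician visits) and program-related costs over 36 weeks".

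The two comparators have different roles under Interventions. For telephone coaching: "The telephone-based coaching walking program will act as a comparative effectiveness control group". For yoga: "The chair-based yoga program will act as an attention control group". The article adds: "Chair-based yoga programs are typically reserved for older adults who are unable to participate in regular exercise or standing yoga programs". The Background says that preclinical mobility limitation "is not typically identified or acted upon by clinicians". The Sample Size section expects "minimal to no change in the chair-based yoga group (0 m/s), small but meaningful change in the telephone-based coaching walking group (0.05 m/s") and 0.12 m/s with Stepping Up.

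**The concern.** An attention control equalises contact time so that the specific effect of Stepping Up can be isolated. That suits the efficacy question. The payer's question is different: what does it cost, and what is gained, if Stepping Up is funded in place of the best alternative? If the cost of running yoga classes is subtracted, Stepping Up is credited with a saving that the payer would make only if it were otherwise funding those classes. Nothing in the article says that it would.

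The three programmes are also mutually exclusive options for the same person. The article sets Stepping Up against the two controls, ranks neither contrast and describes no joint comparison. The Conclusions aim to say whether the programme could be a model for cost-effective programming. A favourable ratio against yoga could carry that statement although another option is the relevant comparator.

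**Working it through.** **The plan's own figures.** The article gives no wage, unit cost or expected QALY, so there is no cost figure to reproduce. The gait-speed effects used below come from the sample-size paragraph, which does reproduce. A one-way analysis of variance on change scores, with SD of change 0.22 × √(2 × (1 − 0.5)) = 0.22 and means 0, 0.05 and 0.12, has 80.5% power at 66 per group.

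**Staff time (Interventions; class size from Recruitment).**
- Stepping Up: "Participants will attend two 1-hour synchronous online sessions (1-hour exercise and 1-hour SM) per week using Zoom", for 12 weeks. An instructor and a physiotherapist attend the exercise hour, and a physiotherapist leads the self-management hour. Per class: 12 instructor + 24 physiotherapist = 36 staff hours.
- Yoga: two instructor-led hours a week for 12 weeks = 24 instructor hours per class.
- Telephone: one call of 20–30 minutes, then 11 weekly calls of about 10 minutes = 130–140 physiotherapist minutes per person.
- Class size n: 5 to 7.

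**Assumption.** Let p be the physiotherapist-to-instructor hourly wage ratio, which the article does not give. Costs are in instructor-hour units and cover staff time only:
- Stepping Up: (12 + 24p)/n per person
- Yoga: 24/n per person
- Telephone: 2.17p to 2.33p per person

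**Share of Stepping Up's staff cost offset by yoga** = 24/(12 + 24p), whatever the class size:

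| p | Share |
|---|---|
| 1 | 24/36 = 67% |
| 1.5 | 24/48 = 50% |
| 2 | 24/60 = 40% |
| 3 | 24/84 = 29% |

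Only the first row follows from the article's hours without a wage assumption beyond equal pay.

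**Illustrative ratios.** Delivery cost per 1 m/s gained, with effects 0, 0.05 and 0.12 m/s standing in for the unknown QALY effects:
- Against yoga: (Stepping Up − yoga)/0.12
- Against telephone: (Stepping Up − telephone)/(0.12 − 0.05)

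| p, n, telephone minutes | Against yoga | Against telephone | Telephone ÷ yoga |
|---|---|---|---|
| 1, 5, 130 | (7.20 − 4.80)/0.12 = 20.0 | (7.20 − 2.17)/0.07 = 71.9 | 3.6 |
| 1.5, 6, 130 | (8.00 − 4.00)/0.12 = 33.3 | (8.00 − 3.25)/0.07 = 67.9 | 2.0 |
| 2, 6, 140 | (10.00 − 4.00)/0.12 = 50.0 | (10.00 − 4.67)/0.07 = 76.2 | 1.5 |
| 2, 7, 140 | (8.57 − 3.43)/0.12 = 42.9 | (8.57 − 4.67)/0.07 = 55.8 | 1.3 |

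For p from 1 to 2, n from 5 to 7 and 130 or 140 minutes, the last column runs from 1.3 to 3.6. At p = 3 with classes of 7 and 140 minutes it reaches 1.0.

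**Is yoga dominated by telephone?** On these effects it is, if telephone also costs less. That requires p below 24/(2.33n) to 24/(2.17n): about 2.06–2.22 for n = 5, 1.71–1.85 for n = 6 and 1.47–1.58 for n = 7. At p = 2, telephone costs 4.33–4.67 against yoga's 4.00 (n = 6) or 3.43 (n = 7), so yoga is then the cheaper option and is not dominated. Telephone is not extendedly dominated there either. At p = 2 and n = 6, telephone against yoga costs 7–13 per m/s, and Stepping Up against telephone costs 76–81. On these assumptions telephone is therefore the next-best comparator for Stepping Up throughout p = 1 to 2, whether or not yoga drops out.

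**The case against.** The strongest reply is that nothing is concealed. The sentence that names yoga also names telephone coaching, which the article calls the comparative effectiveness control, so readers will see both contrasts. Reporting every randomised arm is normal, and the article does not rule out a joint analysis. The Conclusions are hedged. This stands against any claim that the plan hides cost. It does not settle which contrast carries the payer conclusion, because the article ranks neither and words the curves as Stepping Up against its controls.

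A reader might go further and infer that yoga is a dominated option. The documents do not support that. The cost half fails at a 2:1 wage ratio for classes of 6 or 7. The effect half borrows gait-speed assumptions made for power, while the analysis uses QALYs, for which no expectation is given. Health-care costs, which are in scope, are left out.

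A reader might also infer that yoga is inert and that current care is no programme. The Interventions section cites a trial in lower-extremity osteoarthritis in which chair yoga reduced pain and raised gait speed, although the gains did not last. The EQ-5D-5L has a pain dimension, so a QALY effect is possible. The Background says only that clinicians do not typically identify or act on the condition.

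Finally, that yoga's own programme cost is charged is the natural reading of the Objectives, but it is not spelled out.

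**Conclusion.** The point holds as a matter of comparator choice. A payer-perspective ratio against an attention control, net of that control's delivery cost, can look more favourable than the ratio against the next-best option. Yoga's staff time offsets 67% of Stepping Up's at equal pay, 40% at 2:1 and 29% at 3:1. These shares count staff time only, and all but the first need a wage ratio that the article does not give. The factor of about 1.3 to 3.6 between the two contrasts is an illustration. It rests on the assumed gait-speed effects, wage ratios of 1 to 2, and no difference in health-care costs. It is not a forecast of the cost per QALY. Whether yoga is dominated depends on wages, class size, QALYs and health-care use, and the trial's data will have to show it.

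**What to change.** 1. In the cost-effectiveness paragraph of the Analysis section, specify a full incremental analysis of the three programmes. Order them by cost, remove dominated and extendedly dominated options, and present multi-option acceptability curves giving the probability that each programme is optimal. State that the payer conclusion rests on this analysis and not on the yoga ratio alone.
2. Add a sensitivity analysis, labelled as such, that repeats the yoga contrast without yoga's programme delivery cost. State that, read as a comparison with no programme, it assumes yoga has no effect on QALYs or health-care use, and that it understates Stepping Up's benefit against no programme if yoga helps.

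The cost is a change of wording and a little extra analysis. No new participants or data are needed, and the article dates the start of analysis to November 2025. The downside is that the headline ratio may be less favourable.

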### Outcomes

Demographic information (birth date, sex, gender, marital status, living accommodation, employment status, education, ethnic origin, and household income) and comorbid conditions (identified using the Self-Administered Comorbidity Questionnaire) [55] will be collected at baseline. Primary and secondary outcomes will be assessed virtually at baseline, 12 weeks, 24 weeks, and 36 weeks. Health care usage data will be collected during follow-up assessments only.

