#### Quality of Life

The EQ-5D-5L is a generic utility-based health related quality of life questionnaire [81] with an MCID of 0.056 [82]. It consists of 5 questions covering the dimensions of mobility, self-care, usual activities, pain and discomfort, and anxiety and depression with 5 response options indicating no, mild, moderate, severe, and extreme problems for each dimension [83]. The EQ-5D-5L can define a total of 3125 health states which can be converted to a utility index anchored at 0 for a state being equal to dead, and 1 for full health using the Canadian Scoring function [84]. The utility index combined with life expectancy allows for the estimation of quality-adjusted life years (QALYs), a recommended generic outcome measure in health economic evaluation in Canada and other countries [85-87].

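### The bootstrap 95% CI is planned on the cost-per-QALY ratio without condition, and it has no meaning if the QALY difference is not clearly above zero

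*Protocol article*

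**What the plan says.** The Analysis section of the protocol article sets up a cost-effectiveness comparison of Stepping Up with each of the two other programs: "The main effectiveness measure for the cost-effectiveness analysis will be the incremental cost per QALY gained over 36 weeks". For sampling uncertainty it states that "nonparametric bootstrap will be used to calculate the 95% CI around the incremental cost per QALY ratio". The next sentence adds a second presentation: "The decision uncertainty will be presented using cost-effectiveness acceptability curves".

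No rule is attached to the ratio interval for replicates in which the QALY difference is zero or negative.

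Other statements that bear on the point:
- **Utility benchmark.** The Quality of Life section describes the EQ-5D-5L as a "generic utility-based health related quality of life questionnaire [81] with an MCID of 0.056". The article gives no expected QALY difference, no utility or QALY SD and no cost SD.
- **Timing.** "Primary and secondary outcomes will be assessed virtually at baseline, 12 weeks, 24 weeks, and 36 weeks".
- **Direction of resource use.** "Our hypothesis is that there will be reduced hospitalizations and physician visits for the intervention group compared with the control groups".
- **Size.** The Sample Size section rests on the 4MGS alone.

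**The concern.** A ratio with a denominator that can pass through zero has no ordinary confidence interval. As the QALY difference approaches zero from above, the ratio runs to plus or minus infinity, depending on the sign of the cost difference. On the other side of zero its sign flips. A negative ratio can then mean cheaper and better (dominant) or dearer and worse (dominated). A positive ratio can mean dearer and better or cheaper and worse. Limits read from an ordered list of such ratios mix opposite conclusions.

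The cost difference may also take either sign. The protocol hypothesises lower health care use, while Stepping Up classes use both a fitness instructor and a physiotherapist, so replicates could land in all four quadrants of the cost-effectiveness plane. At stake is one published interval for each comparison. It could look like an ordinary CI and be read as one when it is not.

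**Working it through.** **Plan's own figures.** The article gives no figure for the QALY or cost analysis, so there is none to reproduce there. The group size used below does reproduce. With correlation 0.5 the SD of change is 0.22·√(2·(1−0.5)) = 0.22. An overall three-group F test with mean changes 0, 0.05 and 0.12 m/s and 66 per group has 80.5% power. Then 66/0.8 = 82.5, rounded up to 83 per group, or 249 in all.

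**Step 1. Size of the QALY difference.** Take equal baselines and a utility gain d that is reached linearly by week 12 and held to week 36. The area is d × (0.5·12 + 24)/52 = d × 30/52.
- Full MCID: 0.056 × 30/52 = 0.0323
- Half MCID: 0.028 × 30/52 = 0.0162
- Quarter MCID: 0.014 × 30/52 = 0.0081

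**Step 2. Standard error.** Assumed, not in the article: QALY SD of 0.06 to 0.08, no baseline adjustment. SE = SD × √(2/n). At n = 66 it is 0.0104 to 0.0139; at n = 83 it is 0.0093 to 0.0124.

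**Step 3. Share of replicates with a negative QALY difference.** By normal approximation this is Φ(−ΔQ/SE), taking the observed difference to equal the assumed one.

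| True gain | ΔQ | 66 per arm | 83 per arm |
|---|---|---|---|
| Full MCID | 0.0323 | 0.1–1.0% | 0.03–0.5% |
| Half MCID | 0.0162 | 6.1–12.3% | 4.1–9.7% |
| Quarter MCID | 0.0081 | 22–28% | 19–26% |

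Rounding the half-MCID gain to 0.016 before dividing gives 6.3 to 12.5%, hence about 6 to 13%. Once the share exceeds 2.5%, a 95% limit for the QALY difference itself lies below zero.

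**Step 4. Wider assumptions.** Let the utility SD run from 0.08 to 0.20, the within-person correlation from 0.5 to 0.7, and n be 66 or 83 per arm (all SDs and correlations assumed). Use a trapezoidal area at weeks 0, 12, 24 and 36. The probability that the 95% CI for the QALY difference includes zero is:

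| True gain | Baseline-adjusted | Unadjusted |
|---|---|---|
| None | 0.95 | 0.95 |
| Quarter MCID | 0.48–0.91 | 0.78–0.93 |
| Half MCID | 0.02–0.77 | 0.35–0.88 |
| Full MCID | 0.00–0.31 | 0.00–0.67 |

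**Step 5. What the ratio interval then looks like.** Illustration with all inputs assumed: QALY difference 0.0162 (SE 0.0118), cost difference 200 (SE 400), independent normals.
- The point ratio is 200/0.0162, about 12,300 per QALY.
- P(ΔQ < 0) = Φ(−0.0162/0.0118) = 0.085, and P(ΔC < 0) = Φ(−200/400) = 0.309.
- Dominant: 0.915 × 0.309 = 0.282. Dominated: 0.085 × 0.691 = 0.059.
- Negative ratios: 0.282 + 0.059 = 0.341, of which 83% are dominant and 17% dominated.
- By simulation, the 2.5th and 97.5th percentiles of the ratio are about −170,000 and +210,000 per QALY.

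The negative limit does not separate the best outcomes from the worst.

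**The case against.** **The article does not say that percentiles of ordered ratios will be used.** It says only nonparametric bootstrap, and a health-economic analysis plan could say how quadrants are handled. This is fair as to detail. But what is to receive the interval is fixed as the ratio, without condition, and the ambiguity lies in the ratio itself. When replicates occupy all four quadrants, the value of the ratio alone cannot rank them.

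**A reader might infer that failure is likely.** The article does not support that. It gives no expected QALY effect and no SD, and the shares in Step 3 hold only if the observed difference equals the assumed one. At a sustained full MCID, negative replicates are at most about 1%, under the 2.5% tail, and the ratio interval would be readable.

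**A reader might infer that the whole uncertainty analysis is unsound.** It is not. The acceptability curves count replicates in which Stepping Up is cost-effective at each willingness-to-pay value, which is well defined in every quadrant. They are the stated vehicle for decision uncertainty.

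**A reader might also infer that QALYs will not be adjusted for baseline utility.** That would rest on the silence of a condensed article. The nearest stated rule points the other way: secondary outcomes, of which the EQ-5D-5L is one, are to be analysed by ANCOVA with their baseline value as covariate. It is not counted as an error here.

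**Conclusion.** The point holds in a limited form. The article commits to a ratio interval that is interpretable only if the QALY difference is clearly positive, and it attaches no such condition. A small QALY difference is plausible over 36 weeks, since even a sustained full MCID yields about 0.032 QALY. The chance that the interval fails ranges from negligible at a sustained full MCID with small SDs to 95% if there is no utility effect. Every figure between those rests on assumed SDs and effects, so the article supports the statement that the interval can fail and not a probability that it will.

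The consequence is minor. It concerns one reported interval per comparison in a secondary economic analysis and leaves the acceptability curves and the primary outcome untouched. A pre-specified method should still work when there is no effect, and this one does not.

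**What to change.** Change the wording of the economic analysis as follows, using the same bootstrap replicates:

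1. Put the bootstrap 95% CI on incremental net monetary benefit, λ·ΔQALY − ΔCost, at willingness-to-pay values λ stated in advance. This is linear in both differences, so it has no break at zero.
2. Report bootstrap 95% CIs for incremental cost and for incremental QALYs separately.
3. Keep the planned acceptability curves.
4. Report the ratio as a point estimate. Add a CI only if the QALY difference is clearly positive, for example if its own bootstrap 95% CI lies wholly above zero. Otherwise describe the result by quadrant.

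The cost is a few lines of text and no new data or resampling. The downside is that the willingness-to-pay values must be chosen and stated beforehand. The article schedules analysis to begin in November 2025, and the change should be fixed before analysis starts.
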